## Abstract

**Background:**

The 23-valent pneumococcal polysaccharide vaccine reduces the risk of pneumonia among adults by 38% to 46%. However, only a few older adults in resource-limited areas of China have received the pneumococcal vaccination. Pay-it-forward is a social innovation that offers participants free or subsidized health services and a community-engaged message, with an opportunity to donate to support subsequent recipients.

**Objective:**

This study aims to assess the effectiveness and cost-effectiveness of the pay-it-forward intervention in encouraging the uptake of the 23-valent pneumococcal polysaccharide vaccine in adults aged ≥60 years.

**Methods:**

A 2-arm, parallel randomized controlled trial will be conducted in 4 community health centers in Nanning city, Guangxi province, China. We will use a block randomization design. A total of 204 older adults will be randomly allocated in a 1:1 ratio to either the pay-it-forward group or the standard-of-care group. Each participant will complete a web-based questionnaire. The standard-of-care group will be required to pay for the vaccine themselves. In contrast, the pay-it-forward group will receive a 150 RMB (US $20.7) vaccination subsidy, postcards, and the opportunity to donate. The participants in both groups will be followed up in the second and fourth weeks after enrollment. The primary outcome will be uptake of the 23-valent pneumococcal polysaccharide vaccine, as determined by administrative data. Secondary outcomes include costs, pneumococcal vaccination knowledge, attitudes toward the vaccine, perceptions of gratitude, incidence of adverse reactions and adverse events, and the likelihood of recommending pneumococcal vaccination to others.

**Results:**

Participant recruitment and follow-up were conducted from January 2024 to September 2024. A total of 220 participants were enrolled. Finalized results are expected in June 2026.

**Conclusions:**

This study will provide evidence on the effectiveness and economic costs of the pay-it-forward strategy for pneumonia vaccination among older adults. The findings could have implications for vaccination policy and offer a new approach for increasing vaccination in resource-limited areas.

**Trial Registration:**

Chinese Clinical Trial Registry ChiCTR2400079410; https://www.chictr.org.cn/showprojEN.html?proj=213999

**International Registered Report Identifier (IRRID):**

DERR1-10.2196/70246

## Introduction

### Background

*Streptococcus**pneumoniae* poses a significant threat to global health, contributing substantially to morbidity and mortality [1,2]. Furthermore, it is recognized as the most prevalent bacterial agent that causes community-acquired pneumonia, a condition associated with increased morbidity, mortality, and economic burden, particularly among individuals aged >65 years [3,4]. Globally, pneumococcal complications were present in 90% of older adults (aged ≥65 years) from 2005 to 2014 [5], with *S*
*pneumoniae*–associated lower respiratory infections responsible for 500,000 deaths (45.74% of global pneumococcal deaths) in those aged ≥70 years in 2016 [6]. The estimated incidence of community-acquired pneumonia among individuals aged ≥60 years in China was 34.68 per 1000 person‐years in 2016 [7]. The in-hospital mortality rate for patients aged ≥65 years with community-acquired pneumonia from January to December 2014 was 5.7% [8]. The disease burden of influenza virus infections is equally severe as pneumonia among older adults. A population-based study demonstrated that adults aged 65 to 74 years experienced influenza-associated excess respiratory mortality rates ranging from 2.9 to 44 per 100,000, while those aged ≥75 years faced even higher rates, ranging from 17.9 to 223.5 per 100,000 [9]. Influenza viruses typically promote secondary pneumococcal infections [10], and their coinfection significantly increases the risk of hospitalization, serious illness, and death [11]. This underscores the need for pneumococcal and influenza vaccines to prevent community-acquired pneumonia and influenza.

The World Health Organization and the Chinese Center for Disease Control and Prevention recommend a 23-valent pneumococcal polysaccharide vaccine (PPSV-23) for adults aged ≥60 years [12]. The PPSV-23 has a 30.9% efficacy in preventing community-acquired pneumonia [13] and offers a 70% protective efficacy against invasive pneumococcal diseases [14]. Furthermore, the vaccine’s protective benefits are known to be durable for up to 5 years [15]. Despite these advantages, the Chinese government has yet to incorporate PPSV-23 into its free routine immunization program for older adults. Consequently, pneumococcal vaccination remains an out-of-pocket service in China (PPSV-23: 220-280 RMB [US $30.4-$38.7] per dose), leading to suboptimal uptake rates among older adults. Only 1% to 42% of older adults in China have received the pneumococcal vaccine [16]. This low uptake of PPSV-23 in China can be attributed to various factors, including financial constraints [17], vaccine hesitancy [18], and poor understanding [19]. Given these challenges, it is imperative to devise and implement innovative strategies to increase PPSV-23 vaccination among older adults.

Pay-it-forward is a socially innovative intervention that promotes health care service use [20]. With pay-it-forward, individuals receive a gift, such as a free or subsidized health care service. They are then invited to donate money or create a postcard with an encouraging message to support subsequent health care service recipients [21]. This intervention may help alleviate financial barriers that hinder the uptake of the PPSV-23. This intervention strategy may also promote positive health outcomes by improving vaccine trust and confidence [22]. Our previous studies have suggested that pay-it-forward interventions significantly increased influenza vaccination among older adults [23] and improved human papillomavirus vaccination among adolescent girls aged 15 to 18 years [24].

However, existing research on pay-it-forward mainly focused on more high-income cities [23,25,26]. Furthermore, no research has focused on using pay-it-forward to promote pneumococcal vaccination. This underscores the importance of exploring pay-it-forward as a strategy to boost PPSV-23 vaccination in resource-limited areas.

Guangxi is recognized as one of the resource-limited provinces in China. In 2022, the per capita disposable income of households in 94 of 111 counties in Guangxi was lower than the national average (US $5091.7) [27,28]. The pay-it-forward intervention may present a potential solution to increase the PPSV-23 vaccination rate among older adults in Guangxi.

### Aims and Hypotheses

This study will use a randomized controlled trial design with the primary objective of evaluating the effectiveness of the pay-it-forward intervention in promoting PPSV-23 vaccination in resource-limited settings. Through this research, we aim to compare vaccination uptake rates between the pay-it-forward and standard-of-care groups, and further assess the cost-effectiveness and per capita costs of both approaches. The findings will provide an innovative intervention model for improving pneumococcal vaccination among older adults in resource-ed-limited areas, offering critical evidence to inform government decisions on vaccine subsidy policies. Our hypotheses are as follows:

1. Pay-it-forward is superior to the standard-of-care in promoting pneumococcal vaccination.

2. The pay-it-forward intervention is associated with lower per capita costs of PPSV-23 vaccination.

## Methods

### Study Design and Setting

We will conduct a 2-arm, parallel randomized controlled trial among adults aged ≥60 years. Community health care centers (CHCs) will be the unit of randomization and intervention. We will recruit participants via vaccination clinics, WeChat (Tencent Technology Company Limited), and SMS text messaging. Participants will be randomly allocated to either the standard-of-care arm (self-payment for vaccinations) or the pay-it-forward arm (receiving a 150 RMB [US $20.7] subsidy for vaccination and opportunities for donation and handwritten postcards) in a 1:1 ratio through an envelope randomization mechanism, with blocks of 4 participants per group. Follow-ups are planned for the second and fourth weeks after enrollment of participants. At the end of the fourth-week follow-up, we will confirm the number of individuals vaccinated with the PPSV-23 in both groups through the vaccination information management system for the immunization program. Written informed consent will be obtained from each participant before enrollment. The CHCs are the central vaccination units for residents and have sufficient vaccine supplies and medical staff familiar with vaccination procedures, facilitating the recruitment of study participants. To ensure sample representativeness, we plan to conduct this study in Qingxiu district (high-income areas), Xixiangtang district (middle-income area), and Liangqing district (low-income area) in Nanning city, Guangxi province. All research assistants and community health care workers (CHWs) involved in this study will receive the same training. Figure 1 and Table 1 illustrate the study design and interventions.

**Figure 1 figure1:**
[figure not shown]
Framework diagram of the study. PIF: pay-it-forward; PPSV-23: 23-valent pneumococcal polysaccharide vaccine.

**Table 1 table1:** Schedule of events of the pay-it-forward for 23-valent pneumococcal polysaccharide vaccine (PPSV-23) study.

Event			Eligibility screening		Enrollment		Follow-up				Closeout
			Week 0		Week 0 (baseline)		Week 2		Week 4		Week 5
**Recruitment and enrollment**											
	Vaccination platform screening	✓									
	Phone or WeChat consultation	✓									
	Recruitment poster			✓							
**Intervention**											
	Pay-it-forward program leaflet			✓							
	PPSV-23 vaccination leaflet			✓							
	PPSV-23 promotional video			✓							
	Informed consent			✓							
	Group allocation			✓							
	Donation			✓							
	Handwritten postcard			✓							
	Baseline questionnaire			✓							
	Follow-up questionnaire					✓		✓			
**Assessment**											
	PPSV-23 vaccination rate									✓	
	Vaccination attitudes									✓	
	Willingness to vaccinate									✓	
	Perceptions of gratitude									✓	
	Recommendation of PPSV-23 vaccination									✓	
	Incidence of adverse events or reactions to vaccination							✓			
	Cost-effectiveness										

### Public Involvement Framework and Participant Recruitment

The public will be involved in creating project materials, such as developing a video explaining the concept of pay-it-forward, co-designing postcards to promote PPSV-23 vaccination [23], and discussing how to describe the pay-it-forward intervention to the participants.

To achieve the target sample size within the planned recruitment period, we will adopt multiple proactive recruitment strategies. Eligible participants will be identified and approached through vaccination clinics at participating CHCs, where staff routinely engage with this population. In addition, digital outreach strategies will be used, including invitations via WeChat messages and SMS text messaging notifications sent through local public health networks. The CHC staff will be trained to provide clear, culturally appropriate explanations of the study’s purpose and procedures to encourage participation. The intervention itself—including a 150 RMB (US $20.7) vaccination subsidy and the opportunity to write and receive handwritten postcards—is expected to enhance engagement and reduce financial and psychological barriers to participation. Recruitment progress will be monitored weekly by the coordinating research team. If enrollment falls behind schedule at any site, responsive strategies will include increasing outreach messaging, extending clinic hours, or deploying additional staff to support recruitment efforts.

### Community Engagement

To determine the effectiveness of the PPSV-23 and the benefits of vaccination for community residents, we will cooperate with local CHCs. CHWs will participate in the design of the pneumonia leaflet, refinement of the questionnaire, development of communication strategies, and formulation of recommendations to enhance the engagement of older adults in this study. The participants will also be invited to write postcards for subsequent participants.

### Participants

Eligible participants will be screened for participation in the program with the help of CHC health care workers. Inclusion criteria are as follows: (1) aged ≥60 years; (2) meeting the medical requirements for PPSV-23 vaccination; (3) residing in the community for the past 3 months; and (4) mentally capable of providing informed consent for vaccination. The participants will be excluded if they meet any of the following criteria: (1) older adults having severe chronic or psychiatric illnesses; (2) older adults having a clinically evaluated risk of allergy to PPSV-23; and (3) older adults having received PPSV-23 within the past 5 years.

### Randomization

This study will use block randomization to ensure balance between the intervention and control groups (block size=4). First, random sequences will be generated by computer from random seeds using SPSS software (version 25.0; IBM Corp). Each set of 4 random numbers will be grouped as a block and numbered in the order of generation. Subsequently, the random numbers within each block will be arranged in ascending order. The 2 smallest numbers will be assigned to the standard-of-care arm, and the 2 largest will be assigned to the pay-it-forward arm. Afterward, the study designer will write the corresponding numbers on the surface of opaque envelopes, insert the intervention material and group assignment information, and seal them. The participants will receive the envelopes corresponding to their assigned numbers and proceed with participation in the study.

### Blinding

Because both study researchers and participants are aware of the intervention allocation, achieving blinding poses a challenge. Nonetheless, several blinding techniques will be used to mitigate bias: (1) strict confidentiality regarding the generation and assignment of random numbers will be maintained among all the participants, research assistants, and CHWs, with only the study designer having access to this information; (2) the research assistants or CHWs responsible for allocating envelopes and interacting with participants will not be informed of the group information until the envelopes are opened; (3) the vaccine nurse will remain unaware of the grouping of participants; and (4) data analysts will be blinded of the intervention received by participants.

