#### Standard-of-Care Group

The participants in this group will also receive the same PPSV-23 vaccination leaflet, a promotional video, and a questionnaire (not including questions on pay-it-forward) similar to that provided to the pay-it-forward group. They will also be informed of the standard cost of the PPSV-23 vaccination (US $29.5-$30). After watching the PPSV-23 promotional video, the participants will be surveyed by a research assistant using questionnaire A and informed that they will need to pay for the vaccination at the standard market price. Participants who are willing to be vaccinated will be assessed for eligibility and scheduled for an appointment for vaccination. The CHW will also follow up with the participants in the second and fourth weeks after enrollment. The participants will receive 100 RMB (US $13.8) for completing the 3 surveys. The participants in the standard-of-care arm will not receive any information about pay-it-forward.

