### Data Collection and Management

When participants are enrolled, the research assistants will record their enrollment time, envelope number, name, identification number, and group. Data will be collected on the professional Chinese questionnaire website Wenjuanxing [29] using self-designed questionnaires, including the baseline questionnaire (questionnaire A) and the follow-up questionnaires (questionnaires B and C). The information collected is presented in Table 2.

**Table 2 table2:** Summary of information to be collected.

Item	Questionnaire codes
Sociodemographics	A
Knowledge about PPSV-23^a^	A, B, and C
Dissemination of PPSV-23	A
Attitudes toward PPSV-23	A, B, and C
Gratitude (GQ-6^b^ scale)	A, B, and C
Willingness and reasons for receiving the PPSV-23	A
Feasibility, appropriateness, and acceptability of pay-it-forward (only pay-it-forward group)	A
Reasons for promoting or discouraging donations (only pay-it-forward group)	B and C
Incidence of adverse reactions or adverse events	B and C
Recommendation of PPSV-23 to others	B and C

^a^PPSV-23: 23-valent pneumococcal polysaccharide vaccine.

^b^GQ-6: Gratitude Questionnaire—6-item scale.

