The uptake of PPSV-23 will be verified using the immunization program’s information management system. Separate questionnaires will be administered to participants in the standard-of-care and pay-it-forward groups. Quality control questions have been included to ensure the accuracy of questionnaire completion. Two similar questions will be included in different sections of the questionnaire to assess the consistency of responses: (1) Does vaccination with PPSV-23 reduce hospitalization and deaths? and (2) Vaccination with PPSV-23 reduces hospitalization and death. If participants respond differently to these 2 similar questions, the questionnaire will be considered invalid, and they will be asked to complete it again. Once participants are enrolled, personally identifiable information and survey data will be entered into an electronic Microsoft Excel form. The form will be password-protected by the study designer, and only the study designer and the researcher responsible for data analysis will have access to it. A data safety and oversight committee will be established, comprising 2 clinicians, an epidemiologist and statistician, and a representative of the medical ethics committee, who will operate independently of the research team. The data safety and oversight committee will review the process of the study, data collection, data management, and analysis. Each participant will be assisted by a CHW in completing the survey. For older adults who do not have a smartphone, the survey will be completed using an electronic device provided by the research program, and the CHW will guide them through the QR code scanning and submission process.

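### The Blinding section says analysts are blinded, but the data-access rule opens survey data that reveal the arm to the researcher doing the analysis, so analyst blinding is not secured as written

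*Protocol article*

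**What the plan says.** The Blinding section concedes that participants and researchers will know the allocation, then lists four measures against bias. The fourth is that "data analysts will be blinded of the intervention received by participants". The first keeps the random assignments with the study designer alone.

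Data Collection and Management describes the data flow. At enrollment "the research assistants will record their enrollment time, envelope number, name, identification number, and group". Later, "personally identifiable information and survey data will be entered into an electronic Microsoft Excel form", and of that password-protected form it says that "only the study designer and the researcher responsible for data analysis will have access to it".

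The questionnaires differ by arm. The same section states that "Separate questionnaires will be administered to participants in the standard-of-care and pay-it-forward groups", and the Standard-of-Care Group section describes "a questionnaire (not including questions on pay-it-forward) similar to that provided to the pay-it-forward group". Table 2 marks two sets of items as belonging to one arm: "Feasibility, appropriateness, and acceptability of pay-it-forward (only pay-it-forward group") in questionnaire A, and "Reasons for promoting or discouraging donations (only pay-it-forward group") in questionnaires B and C.

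**The concern.** A stated safeguard is undone by an access rule elsewhere in the same article. This is more than a detail left to a fuller document: the article makes a positive claim and then describes data handling that, taken at its word, defeats it.

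The stake is analyst discretion. On this text some analysis choices are open, and an analyst who knows the arms could make them with that knowledge. Readers of the results would also credit the trial with a blinded analysis that the described data handling does not support.

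**Working it through.** The plan gives no figure on this point, so the main check sets the sections side by side.

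1. **Who can open the form.** Two people: the study designer and the researcher in charge of the analysis (Data Collection and Management). The designer holds the assignments (Blinding, first measure), so is unblinded by design. Any blinding has to rest on the second person.
2. **What the form holds.** Identifiers and survey data.
3. **Whether the contents reveal the arm.**
   - Identifiers alone do not.
   - The group field would, but the article does not say that it is carried from the enrollment record into this form.
   - The survey data do. Feasibility, appropriateness and acceptability items (questionnaire A) and donation-reason items (B and C) are put to one arm only. A record with those items answered belongs to pay-it-forward; a record from a questionnaire that lacks them belongs to standard of care. No group column is needed.
4. **Whether anything described closes the gap.** Ethical Considerations promises anonymized and deidentified data, which protects identity and not arm. The article describes no coded arm label and no extract without the one-arm items.
5. **Which choices are exposed** (Statistical Analysis).

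| Element | What the text fixes | What stays open |
|---|---|---|
| Primary outcome data | Administrative records (Outcome Measures) | Nothing for the analyst to judge |
| Missing primary outcome | Complete cases if under 5% missing; otherwise multiple imputation; sensitivity analyses added | Little |
| Covariates | Crude and adjusted odds ratios both reported | The set itself: sex, age and education appear only as examples |
| Populations | Intention-to-treat and per-protocol both run | Per-protocol exclusions, and emphasis |
| Missing follow-up data | One of two methods | Last observation carried forward or multiple imputation |

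The last row bears on the scales repeated at follow-up, such as knowledge, attitudes and gratitude, which have no administrative source.

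6. **Would coding the arms A and B be enough?** Sample Size assumes 10% uptake, raised by 20. Read as percentage points this gives 30%, and that reading reproduces the plan's own 158: (0.10×0.90 + 0.30×0.70) × (1.960 + 1.282)² / 0.20² = 0.30 × 10.51 / 0.04 = 78.8, so 79 per arm and 158 in total. With 204/2 = 102 per arm, the standard error of the difference is √(0.30/102) = 0.054, and 0.20/0.054 is about 3.7. By the normal approximation the pay-it-forward arm would then show the higher observed uptake with probability above 0.999. In the pilot the contrast was larger still, 23/26 (88%) against 3/26 (12%). An analyst who expects the subsidy to work could therefore guess the code from the primary result. Coding helps only if the open choices are settled first.

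**The case against.** The strongest reply is that the article states who may open a form, not what file the comparisons are run on. A masked extract is a routine data-management step that a condensed article may leave out, and the promise of deidentification shows that some processing beyond the raw form is intended. The article also does not say that the blinded analysts and the researcher with access are the same person. This stands against the inference, which a reader might draw, that the safeguard does not exist or that the published analysis will have been unblinded. The documents show neither. The reply does not remove the conflict: the access rule names the analysis role, and no masking step is stated.

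A reader might also infer that the primary result is at risk. The documents do not support that. The outcome is an administrative record, its missing-data rule is fixed, and any effect of covariate choice would be visible beside the crude odds ratio.

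The remaining open choices may be settled in an analysis plan that is not shown, and prespecification protects better than coding when the uptake difference may give the code away. Both points are right, and the fix reflects them. Finally, an oversight committee independent of the research team, with epidemiological and statistical expertise, reviews data management and analysis. That is a partial check on conduct, but it does not mask the analyst.

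**Conclusion.** The point holds in limited form. The Blinding section and the data-access rule in Data Collection and Management conflict, and analyst blinding is not secured as written. The cause is the one-arm items in the survey data; identifiers alone would not unblind.

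No bias can be quantified. The exposure is small for the primary outcome and confined to the covariate set and the per-protocol exclusions. It is greater for self-reported secondary outcomes, where the missing-data method is also open.

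This assumes that the researcher with access is one of the analysts meant to be blinded, that the form holds the questionnaires as collected, and that no unseen document already provides a masked file or settles these choices. If those provisions exist, a sentence saying so is all that is needed. The matter should be corrected before results are reported, because the statement describes how the evidence was produced and has to be true.

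**What to change.** Amend Data Collection and Management so that the analyst works only from a file exported by the study designer, who already knows the allocation. The file should carry coded arms and leave out identifiers, any group field and all pay-it-forward-only items.

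Before that file is analysed, fix in writing the covariates, the per-protocol population and the missing-data method for the secondary outcomes. Analyse the pay-it-forward-only items after the comparative analyses are complete.

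Recruitment and follow-up ended in September 2024 and final results are expected in June 2026. The article does not say whether the analyst has yet opened the form. If that has happened, withdraw the fourth measure in the Blinding section and report the analysis as unblinded; fixing any choices not yet made is still worthwhile.

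The cost is one export step by existing staff, a short dated record of the analysis choices, and a change of wording. No further data or participants are needed.
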